## Abstract

**Background:**

Major depressive disorder (MDD) is prevalent, yet sub-optimally treated among persons with multiple sclerosis (MS). We propose that exercise training may be a promising approach for treating depression in persons with MS who have MDD. Our primary hypothesis predicts a reduction in depression severity immediately after an exercise training intervention compared with minimal change in an attention control condition, and the reduction will be maintained during a follow-up period.

**Methods:**

This study involves a parallel-group, assessor-blinded RCT that examines the effect of a 4-month home-based exercise training intervention on depression severity in a sample of persons with MS who have MDD based on the MINI International Neuropsychiatric Interview. The primary outcomes of depression severity are the Patient Health Questionnaire-9 and Hamilton Depression Rating Scale. Participants (*N* = 146) will be recruited from within 200 miles of the University of Illinois at Chicago and randomized (1:1) into either a home-based exercise training condition or control condition with concealed allocation. The exercise training and social-contact, attention control (i.e., stretching) conditions will be delivered remotely over a 4-month period and supported through eight, 1:1 Zoom-based behavioral coaching sessions guided by social-cognitive theory and conducted by persons who are uninvolved in screening, recruitment, random assignment, and outcome assessment. We will collect outcome data at 0, 4 and 8 months using treatment-blinded assessors, and data analyses will involve intent-to-treat principles.

**Discussion:**

If successful, the proposed study will provide the first Class I evidence supporting a home-based exercise training program for treating MDD in persons with MS. This is critical as exercise training would likely have positive secondary effects on symptoms, cognition, and quality of life, and provide a powerful, behavioral approach for managing the many negative outcomes of MDD in MS. The program in the proposed research is accessible and scalable for broad treatment of depression in MS, and provides the potential for integration in the clinical management of MS.

**Trial registration:**

The trial was registered on September 10, 2021 at clinicaltrials.gov with the identifier NCT05051618. The registration occurred before we initiated recruitment on June 2, 2023

**Supplementary Information:**

The online version contains supplementary material available at 10.1186/s12883-024-03634-y.

## Introduction

Multiple sclerosis (MS) is an immune-mediated, neurodegenerative disease of the central nervous system (CNS). There are an estimated one million adults living with MS in the United States [1]. This disease is characterized by demyelination and transection of axons and loss of neurons in the CNS [2]. The extent and location of CNS damage results in consequences including motor and cognitive dysfunction, fatigue, and major depressive disorder (MDD) [3].

MDD is characterized by persistently depressed mood or loss of interest in usual activities plus the presence of at least 5 of 9 symptoms that cause significant impairment in daily life [4]. The prevalence of MDD in persons with MS is nearly 1.7 times higher than the general population [5]. One recent systematic review reported the prevalence of MDD among persons with MS as 23.7% [6] and this translates into an estimated 250,000 people living with MS and MDD in the United States.

MDD has widespread, negative effects on the lives of people with MS [3]. The presence of MDD is associated with worsening of other symptoms such as fatigue, poorer neuropsychological functioning, and lower health-related quality of life (HRQOL) [3].

The prevalence and burden of MDD in MS underscore the critical importance of efficacious antidepressant treatments, yet such treatments are sorely lacking in MS. For example, the American Academy of Neurology concluded that there is insufficient evidence from randomized controlled trials (RCTs) for recommending antidepressants for treating MDD in MS [7]. One meta-analysis [8] of RCTs concluded that “CBT can be an effective intervention for reducing moderate depression, over the short term in patients with MS.” Yet, nearly 50% of participants do not benefit from CBT [9].

Exercise training is a promising therapy for improving depressive symptomology and managing MDD in MS [10]. Exercise training has yielded a moderate-to-large antidepressant effect in persons from the general population who have MDD [11–14]. Exercise training further has improved depressive symptomology in MS [15–17], and those meta-analyses offer critical insights for informing the exercise training parameters for treating MDD. The first meta-analysis indicated that both aerobic and resistance exercise training can yield a reduction in depressive symptoms for people with MS [15]. The second meta-analysis quantified the effect of exercise on depression in adults with neurologic disorders, including MS [16], and noted that interventions meeting physical activity guidelines yielded a reduction in depression that was two-times larger than interventions that did not meet physical activity guidelines. The third meta-analysis examined variables that moderate the effects of exercise on depressive symptoms among people with MS [17], and there was a dose–response effect for frequency (days/week) of exercise on reductions in depressive symptoms with the largest effect occurring for three days/week of exercise training.

The aforementioned meta-analyses identified four major limitations of previous research on exercise training for treating depression in MS [15–17]. The most pressing limitation is that the samples of persons with MS were not pre-screened for MDD [15–17]. Another limitation is that the exercise training programs were administered in supervised, center-based settings that present barriers associated with accessibility (e.g., distance, transportation, and costs) that likely influence adoption and maintenance of exercise behavior. An additional limitation is the lack of standardization of the exercise training prescription included in RCTs. The final limitation is the lack of follow-up regarding the durability of changes in depressive symptoms following exercise training.

We designed a RCT that is based on sound scientific rationale established through critical review and analysis of the relevant literature [10, 15–17], and further capitalizes on our experiences with home-based delivery of exercise training programs in MS [18–22]. To that end, we propose a parallel group, RCT for examining the efficacy of a home-based, exercise training program informed by prescriptive guidelines [23, 24] and guided by social cognitive theory (SCT)-based remote behavior coaching compared with a social-contact, attention control condition (i.e., stretching) for yielding immediate and sustained reductions in the severity of depressive symptoms among persons with MS who have MDD.

## Methods/design

There is only one protocol version and it will follow the Standard Protocol Items: Recommendations for Interventional Trials (SPIRIT) guidelines.

### Aims, design, and setting of the study

The primary aim examines the efficacy of a 4-month, home-based aerobic and resistance exercise training intervention compared with a 4-month, home-based stretching and flexibility intervention (i.e., social contact, attention control condition) for immediate and sustained (i.e., 4-months post-intervention) reductions in depression severity among persons with MS who have impaired MDD.

The secondary aim examines the efficacy of the exercise training intervention compared with the control condition for immediate and sustained improvements in fatigue, cognition, and HRQOL among persons with MS who have impaired MDD.

The tertiary aim involves a manipulation check and examines the efficacy of the exercise training intervention compared with control condition for immediate and sustained improvements in exercise behavior, physical activity, aerobic fitness, and muscle strength for persons with MS who have impaired MDD.

The study aims will be tested using a parallel-group, assessor-blinded RCT design. This study does not include a data safety monitoring board, but there is a data safety monitoring plan and safety monitor for oversight.

### Participants

#### Recruitment

We will recruit participants residing within 200 miles of the University of Illinois Chicago (UIC) campus located in Chicago, IL USA through distribution of study materials (flyers, business and post cards, and advertisements) among the Greater Illinois and other regional Chapters of the National MS Society; North American Research Committee on Multiple Sclerosis and iCONQUER MS Registries; waiting rooms of 10 + local MS Centers and Neurology offices; local community centers, churches, libraries, and physical therapy clinics; community events and MS support group meetings; focal study website (https://metsforms.ahs.uic.edu); UIC and professional listservs; and social media.

##### Inclusion/exclusion

We will assess inclusion/exclusion during a scripted phone screening by the project coordinator, and this will involve a two-stage process with the inclusion and exclusion criteria listed in Table 1.

**Table 1 Tab1:** Inclusion and exclusion criteria by screen

Inclusion criteria	Exclusion criteria
Screen 1: First Level Criteria	
Physician-confirmed diagnosis of multiple sclerosis	High risk for contraindications of possible injury or death when undertaking strenuous or maximal exercise using the Physical Activity Readiness Questionnaire [25]
Relapse and steroid free in the past 30 days	Severe cognitive impairment based on Modified Telephone Interview for Cognitive Status score of less than 18 [26]
Internet and email access	Current high suicidal risk based on the Columbia-Suicide Severity Rating Scale screening version-recent [27]
Willingness to complete the testing and questionnaires, wear the accelerometer, undergo randomization, and engage in exercise training	
Insufficient physical activity based on a Health Contribution Score of less than 14 units from the Godin Leisure-Time Exercise Questionnaire [28]	
Ability to ambulate without assistance and Patient-Determined Disease Steps score between 0 and 2 (i.e., mild ambulatory disability) [29]	
Age between 18 and 64 years	
English as a primary language	
Not pregnant and/or nursing	
Presence of mild or more severe depressive symptoms based on Beck Depression Inventory – Fast Screen score of 4 or greater [30, 31]	
Screen 2: Second Level Criteria	
Major Depressive Disorder based on the MINI International Neuropsychiatric Interview [32]	Other severe mental illness (obsessive–compulsive disorder, schizophrenia, bipolar or other psychotic disorders, or recent or current addiction) as indicated by the MINI [32]

#### Attrition

We have experienced low attrition (10%) in our previous RCTs of the exercise training protocol in this proposal [19], and we note recent data from a meta-analysis suggesting an attrition rate of ~ 10% across 40 RCTs of exercise training in MS [33]. We believe attrition could be higher in this RCT based on depressive symptomology in MDD resulting in poor motivation and adherence for exercise engagement. We conservatively planned for a higher attrition rate of 20% for the proposed RCT, and recognize that retention might be a challenge, although we are including SCT-based content and 1:1 zoom-based behavioral coaching for maximizing retention and adherence [34] as is appropriate for persons with MS who have elevated depressive symptoms [35].

#### Power analysis and sample size

The power analysis was conducted in G*Power, Version 3.1 using F test for Test family and ANOVA: Repeated measures, within-between interaction for Statistical test. We estimated the sample necessary for detecting a Condition (2 levels of between-subjects factor: Intervention vs. Control) × Time (2 levels of within-subjects factor: 0 and 4 months) interaction on the primary outcomes of depression severity (i.e., 9-item Patient Health Questionnaire (PHQ-9; [36]) and Hamilton Depression Rating Scale (HDRS-17; [37]). We did not include 3 time-points as this assumes linear change across all 3 time points in G*Power 3.1, and we expected change between 0 and 4 months for the intervention condition, followed by stability between 4 and 8 months. The effect size (Cohen’s *f* = 0.18) was from our previous meta-analyses [15] regarding the effect of exercise training on depressive symptoms in persons with MS. The power analysis included assumptions of reliability for the within-subjects factor of ICC = 0.50, two-tailed *α* = 0.025, and *β* = 0.05 (i.e., 95% power); the *α* = 0.025 was selected based on two primary outcomes. The power analysis indicated the minimal total sample size for testing the Time × Condition interaction of 122 participants (61 per group), and we anticipate a dropout rate of ~ 20% resulting in a projected recruitment of 146 participants.

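### Recruiting 146 does not preserve the stated minimum of 122 participants at the planned 20% attrition; the effect on power is small

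*Protocol article*

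**What the plan says.** The section on power and sample size describes a G*Power calculation, "ANOVA: Repeated measures, within-between interaction for Statistical test", with two conditions and two time points (0 and 4 months). Its inputs are Cohen's f = 0.18, a two-tailed α of 0.025 for each of the two primary outcomes, 95% power, and "assumptions of reliability for the within-subjects factor of ICC = 0.50". It reports a minimum total of 122, or 61 per group. It then allows for dropout of roughly 20%, "resulting in a projected recruitment of 146 participants".

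The Attrition section gives the same rate without the approximation sign: "We conservatively planned for a higher attrition rate of 20% for the proposed RCT". The comparison there is with attrition of about 10% in the team's own trials and in a meta-analysis of 40 exercise trials in MS. The abstract and the Procedure section repeat the total of 146.

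Under Data analyses, the primary analysis is by intent to treat, using a linear mixed model fitted by REML with subject as a random effect. Analysis of completers is exploratory.

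**The concern.** An attrition rate is a fraction of those randomised. An allowance for 20% attrition should therefore leave the required number after one fifth of the randomised participants are lost. Here it does not: the minimum, the attrition rate and the recruitment target cannot all be true.

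What is at stake is mainly whether the sample-size statement can be relied on. A trial running at 17% to 20% attrition would look to be within plan while holding fewer than the declared minimum of completers. The protocol itself expects that depressive symptoms may raise attrition above past experience, so this range is a realistic one. The Discussion also says that these data would be used to power a Phase III trial, and the same allowance could be carried into that design.

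**Working it through.** **Inputs, all from the protocol.** f = 0.18; correlation between repeated measures ρ = 0.50; α = 0.025; m = 2 time points; 2 groups, allocated 1:1; minimum N = 122; attrition 20%; recruitment 146.

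**1. Reproduce the 122.** For the interaction test, the noncentrality is λ = f² × N × m/(1 − ρ), with 1 and N − 2 degrees of freedom.
- N = 122: λ = 0.0324 × 122 × 2/0.50 = 15.81, power 95.5%.
- N = 120: λ = 15.55, power 95.2%. This is the smallest equal-arm total that reaches 95%.

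The stated 122 is therefore reproduced to within two participants, and the inputs have been read as intended.

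**2. Reproduce the 146.**
- 122 × 1.2 = 146.4, which rounds to 146 and matches.
- 122/(1 − 0.20) = 152.5, so 153, or 154 (77 per arm) for equal arms. This does not match.

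The multiplication by 1.2 is an inference, because the protocol shows no formula. The forward check below does not depend on it.

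**3. Check forward.**
- 146 × 0.80 = 116.8, about 117 completers.
- 122 − 117 = 5 short of the stated minimum.
- Attrition at which 146 still leaves 122: 1 − 122/146 = 0.164, or 16.4%.

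**4. Power on completers only.** At N = 117, λ = 0.0324 × 117 × 2/0.50 = 15.16 and power is 94.6%. That is 0.9 points below the value at 122 and 0.4 points below the 95% target.

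**5. Power under the planned mixed model.** The model keeps the baseline scores of participants who drop out. Take 73 randomised per arm, of whom 73 × 0.80 = 58.4 have 4-month data, and assume the rest are missing at random. In units of the outcome variance, the variance of one arm's estimated mean change is

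(1 − ρ²)/58.4 + (1 − ρ)²/73 = 0.75/58.4 + 0.25/73 = 0.01627.

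With complete data on k participants per arm it is 2(1 − ρ)/k = 1/k. Equating the two gives k = 1/0.01627 = 61.5 per arm, an effective total of about 123. Then λ = 0.0324 × 123 × 2/0.50 = 15.94 and power is about 95.6%. A simulation of the random-intercept REML model (8,000 runs, 146 randomised, 29 without 4-month data) also gave 95.6%; a completers-only test on the same simulated data gave 94.4%.

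**6. Sensitivity of the effective total to ρ.** The same formula gives:
- ρ = 0.40: 2 × 1.2/(0.84/58.4 + 0.36/73) = 124.3.
- ρ = 0.60: 2 × 0.8/(0.64/58.4 + 0.16/73) = 121.7.

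The effective total stays close to 122 across this range.

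**The case against.** The strongest reply is that the completer count is the wrong yardstick. The primary analysis includes everyone randomised, and the mixed model draws some information from the baseline scores of those who leave. Step 5 bears this out: at 20% attrition, 146 randomised are worth about 123 complete participants for the 0-to-4-month contrast on which the trial is powered. A reader might infer from the shortfall of 5 that the trial misses its 95% power at the planned attrition. The documents do not support that reading. The 94.6% belongs to an analysis that the protocol treats as exploratory, and the planned analysis keeps about 95.6% under the stated assumptions.

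Three smaller replies also carry some weight. The sample-size section writes the dropout rate as approximate, but the Attrition section states 20% plainly, and 146 fits only 16.4%. The 122 already exceeds the recomputed 120 by two, so the practical gap on completers is about three. And the planned allowance is still cautious relative to the cited experience: at 10% attrition, 146 leaves 146 × 0.90 = 131 completers.

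None of this makes the stated figures agree. The protocol chose to inflate a fixed minimum for dropout, and the inflated number does not restore that minimum at the stated rate. The gain from the mixed model offsets the consequence, but the protocol does not offer it as the basis for 146.

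**Conclusion.** The point holds as an arithmetic inconsistency of small consequence. At 20% attrition, 146 randomised leave about 117 completers, not 122; preserving 122 would need 153 (154 for equal arms), and 146 does so only up to about 16% attrition. That the cause was multiplication by 1.2 is likely but not documented.

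Power for f = 0.18 is about 94.6% on completers only and about 95.6% under the planned mixed model. The second figure assumes data missing at random, a correlation of 0.50, and the unadjusted contrast between 0 and 4 months. It would be less secure if dropout depended on unobserved depression severity, which is conceivable in this population. It would be wrong to conclude that the trial is underpowered at its planned effect size, or that enrolment has to rise.

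**What to change.** Keep 146 and restate the end of the sample-size section along these lines: 146 randomised gives about 117 completers at 20% attrition; 122 completers are retained only if attrition does not exceed about 16%. Power for f = 0.18 at 20% attrition is about 94.6% on completers only, and about 95% under the intent-to-treat mixed model assuming data missing at random.

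The cost is a short wording change. It adds no participants, leaves the analysis as it is, and gives the team the attrition level at which the completer count would fall below 122.

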### Outcomes

#### Overview

The primary outcomes are the PHQ-9 [36] and HDRS-17 [37] as measures of depression symptom severity appropriate for MDD, whereas the secondary outcomes include measures of fatigue, cognitive performance, and HRQOL. The tertiary outcomes are exercise behavior, accelerometry as a device-based measure of free-living PA, and aerobic and muscle fitness. All outcomes will be assessed at baseline (0 months), immediate follow-up (4 months), and long-term follow-up (8 months) by treatment-blinded assessors. The assessors will not be involved in random assignment or delivery of the conditions, and will not directly communicate with the behavior coaches about participants. Participants themselves will be instructed not to discuss exercise routines with assessors, and why it might bias the evaluators.

#### Primary outcome measures

We include two outcomes for depression severity, as one is self-reported (primary) and the other is a semi-structured, interviewer-rated measure (secondary). The logic is that the self-report change in depression severity should be confirmed with the semi-structured, interviewer-rated change, as change in the former is more likely, but could represent a self-report bias associated with participants not being blinded regarding treatment condition.

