### Data analyses

#### Overview

The data analyses will be overseen by a biostatistician and follow intent-to-treat (ITT) principles (i.e., include all persons regardless of dropout). We will perform exploratory data analyses only among those who complete immediate and long-term follow-up testing (i.e., completer’s or per protocol analysis). We will check the data for errors and outliers, and lock the data set before analyses. The analytic plan will account for potential confounders of the intervention effect on the outcomes. The confounders may include MS duration, BMI, age, sex, disease-modifying therapy, and relapse rate. We will include any of those variables and others that differ between conditions as covariates in the following analyses.

#### Data analysis – aim 1

The first analysis tests the hypothesis that those who are randomly assigned into the intervention condition (i.e., exercise training) will demonstrate (a) reductions from baseline in depression severity that (b) are sustained over 4-months of follow-up compared with those in the control condition (i.e., stretching). The hypothesis will be tested using a linear mixed model in JMP Pro 16.0. The linear mixed model will include condition and time as fixed effects, and subject nested within condition as a random effect using unbounded variance components and the REML method (https://www.jmp.com/content/dam/jmp/documents/en/academic/learning-library/08-repeated-measures-analysis-(mixed-model).pdf). The hypothesized interaction term will be decomposed with follow-up tests, and differences in comparison of mean scores will be expressed as Cohen’s d with standard guidelines for interpretation. The final models for PHQ-9 and HDRS-17 scores will be adjusted for covariates. The overall Type I error will be controlled based on an adjustment of alpha (two-tailed *α* = 0.025) given the two primary outcomes in Aim 1.

#### Data analysis – aim 2

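### The two depression outcomes are co-primary with split alpha in three sections but ranked, with one confirming the other, in a fourth, so a result positive on PHQ-9 alone gets two verdicts

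*Protocol article*

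**What the plan says.** Three sections of the protocol article give the two depression outcomes equal rank.

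- Outcomes, Overview: "The primary outcomes are the PHQ-9 [36] and HDRS-17 [37] as measures of depression symptom severity appropriate for MDD". The secondary outcomes listed there are fatigue, cognitive performance and quality of life.
- Power analysis and sample size: the calculation uses "two-tailed *α* = 0.025, and *β* = 0.05 (i.e., 95% power"), and the 0.025 level "was selected based on two primary outcomes".
- Data analysis – aim 1: "The overall Type I error will be controlled based on an adjustment of alpha" to two-tailed 0.025, "given the two primary outcomes in Aim 1".

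The section Primary outcome measures ranks them: "as one is self-reported (primary) and the other is a semi-structured, interviewer-rated measure (secondary"). It then gives the reason for having both: "the self-report change in depression severity should be confirmed with the semi-structured, interviewer-rated change". Its argument is that change on self-report is the likelier of the two, but could be reporting bias in participants who are not blinded to their condition.

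The only decision rule is in the Discussion. It asks for statistically significant and clinically meaningful improvement in the depression outcomes, in the plural, and does not say whether one or both must improve.

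**The concern.** A 0.025/0.025 split is the correction for a claim that either outcome can support. Ranked or confirmatory logic is a different design: if the claim needs both outcomes, each can be tested at 0.05 and the error of the joint claim stays at or below 0.05.

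The conflict bites in the discordant case that the protocol itself foresees, a significant PHQ-9 without a significant interviewer rating. The Aim 1 analysis would count this as a positive primary outcome. The outcome section would call it unconfirmed and possibly biased. With no rule fixed, the verdict could be chosen after the results are known. The stated 95% power also describes neither an either-suffices claim nor a both-required claim; it is the power for one outcome taken alone.

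**Working it through.** **Inputs.** All are from Power analysis and sample size: f = 0.18 (applied to both outcomes), 2 groups, 2 time points (m = 2), within-subject correlation ρ = 0.50, two-sided α = 0.025, power 95%, N = 122 evaluable. The correlation r between the two test statistics is not given; I assume 0 to 0.8.

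**1. The plan's own figure.** For the within-between interaction, λ = f²·N·m/(1 − ρ), with 1 and N − 2 degrees of freedom.

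- At N = 122, λ = 0.0324 × 122 × 2 / 0.5 = 15.81. Power by the non-central F is 95.5% at α = 0.025.
- The smallest even N reaching 95% is 120 (95.2%; N = 118 gives 94.8%).

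The stated 122 is thus reproduced to within two participants, for a single outcome at 0.025.

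**2. One outcome at 0.05.** At N = 122, power is 97.6%, and 95% is reached at N = 104. For PHQ-9 alone, the split therefore costs 97.6 − 95.5 = about 2 points of power, or 120 − 104 = 16 evaluable participants.

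**3. Both or either.** Each test statistic is taken as normal with mean √15.81 = 3.976 and unit variance, with correlation r between the two. The critical values are 2.241 (α = 0.025) and 1.960 (α = 0.05). P(both) is the bivariate normal probability that both exceed the critical value, and P(either) = 2·P(one) − P(both). P(one) is 95.9% at 0.025 and 97.8% at 0.05, slightly above the non-central F values.

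| Rule at N = 122 | r = 0 | r = 0.8 |
|---|---|---|
| Either, each at 0.025 | 99.8% | 98.0% |
| Both, each at 0.025 | 91.9% | 93.7% |
| Both, each at 0.05 | 95.7% | 96.6% |

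At the level the plan uses, the gap between the either and both rules is 99.8 − 91.9 = 7.9 points at r = 0 and 98.0 − 93.7 = 4.3 points at r = 0.8. This is the share of trials, under the plan's assumptions, whose verdict depends on which section is followed. If both are required at 0.025, reaching 95% joint power would take about 136 evaluable participants at r = 0 and 132 at r = 0.7.

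**4. Type I error.**

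- Either at 0.025 each: at most 0.025 + 0.025 = 0.05.
- Both at 0.05 each: at most 0.05, since the claim fails if either test fails.
- Both at 0.025 each: at most 0.025, half of what is available.
- Either at 0.05 each, which no section proposes: 9.75% at r = 0 and 7.0% at r = 0.9. The split is therefore needed if either outcome may carry the claim.

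**The case against.** The strongest reply is that the operative testing text is consistent. The overview, the power section and the Aim 1 analysis all describe a standard two-primary Bonferroni design. The confirmation sentence explains why two measures are taken; it says the change should be confirmed, not that it must be, and no section states a gatekeeping or both-must-win test. This stands in part: it would overstate the text to say that the protocol formally requires confirmation. But the ranking labels and the confirmation rationale sit in the section that defines the primary outcomes, and they point to a different verdict on a PHQ-9-only result.

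A reader might infer that the split simply wastes alpha and should go. The documents do not support that. The split is conservative only under the confirmatory reading; if either outcome suffices, it is correct and must stay.

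A reader might also infer a large loss of power. At a 0.5 SD effect with N = 122 and r = 0.6, both outcomes are significant in 57% of trials at 0.025 and 68% at 0.05, and either in 83% at 0.025. The sample size does not rest on 0.5 SD, which the Discussion gives only as an example of a clinically meaningful difference. On the same change-score scale, f = 0.18 corresponds to 3.976/√(122/4) = 0.72 SD. Most of that drop comes from the smaller effect, which is a separate question.

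**Conclusion.** The contradiction is in the current text and no section resolves it. Its main consequence is an undefined verdict when only one depression outcome is significant. It does not raise the false-positive rate under any reading.

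With the plan's own inputs the effect on power is modest. A both-required claim has about 92% to 94% power at 0.025 each, short of the stated 95%, and about 96% to 97% at 0.05 each. These figures assume 122 evaluable participants, r between 0 and 0.8, a normal approximation and the same f on both outcomes. The last may be generous, because the protocol itself expects change on self-report to be the likelier. Since the point concerns which result decides the trial, it should be settled despite the small numerical cost.

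**What to change.** Before any unblinded analysis, choose one rule and align Outcomes (Overview), Primary outcome measures, Power analysis and sample size, Data analysis – aim 1, and the decision rule in the Discussion.

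- **If the confirmatory logic governs:** claim an antidepressant effect only when both outcomes are significant, each at two-sided 0.05. Drop the split and restate power for the joint claim, with the assumed correlation. No added participants are needed on the plan's inputs.
- **If either outcome may establish efficacy:** keep 0.025 each, and remove the primary/secondary labels and the confirmation wording from Primary outcome measures.

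The cost is wording in these sections. As 18 people had been enrolled and randomized by February 2024 (Current trial status), the change should be a dated amendment that records that no outcome data by condition had been seen. The downside of the both-required rule is that no efficacy claim can then rest on one measure alone, including the blinded assessor's rating if PHQ-9 fails.
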